### Secondary endpoint analysis

Summary statistics will be computed for changes in visual acuity for the two treatment groups at 6 and 12 months and the proportion of patients in each group who suffer any adverse events will be summarised. The exact binomial method will be used to compute 95% confidence intervals. Summary statistics for all other secondary outcomes will be provided by treatment group and if statistical comparisons are made, results will be reported as exploratory.

### Missing data

The sample size calculation assumed 5% of patients would not provide an evaluable 6 month outcome. If data are missing for any patients, reasons for missing data may be important and these will be examined using logistic regression of covariates on an indicator of missing data. An available case analysis will be conducted together with an ITT analysis (using imputation) and results compared in a sensitivity analysis. Any deviations from the statistical analysis plan will be described and justified in the final report, as appropriate.

### Trial documentation and data collection

The CRFs will be designed and produced by the investigators, according to the sponsor’s CRF template. The final version will be approved by the sponsor. It will be the responsibility of the investigators to ensure the accuracy of all data entered onto the CRFs. A delegation log will identify all trial personnel with responsibilities for data collection and handling, including those who have access to the trial database. Data handling will adhere to the Data Protection Act, 1998.

### Ethics and competent authority review

Applications to the UK’s main REC (NRES Committee London – Central) and the local Moorfields Research Management Committee have received favourable opinions and a Clinical Trial Authorisation has been issued by the MHRA.

### Publication policy

The results of this study will be submitted for publication in peer-reviewed medical journals regardless of whether the findings are in favour of the trial intervention.

## Discussion

This randomised controlled trial investigating the use of a sustained-release dexamethasone implant will be the first to evaluate its role as an adjunctive agent, in patients undergoing vitreoretinal surgery for retinal detachment with established PVR.

Our projected recruitment rate is based on a retrospective audit of the incidence of relevant cases at the study site. Due to the poor prognosis associated with current standard treatment, we expect a high recruitment uptake following successful eligibility screening. We remain optimistic that our recruitment target will be met within the projected timescale.

We accept that although our inclusion criteria specifies Grade C PVR requiring surgery with silicone oil, the cohort of participants is likely to be quite a heterogeneous group. The severity of Grade C PVR can vary widely throughout its sub-classification both in terms of extent (number of clock hours) and distribution (focal, diffuse, anterior, posterior or subretinal). However, we expect the adequacy of randomisation to compensate for this and shall acknowledge any unequal weighting within the groups as limitations of the study. We do, however, accept that we may limit our sensitivity to small differences between the two groups.

As this single centre study serves a wide geographical catchment area with a broad patient demographic representative of the UK, we do not expect the results to provide a misleading estimate of treatment effect. Again, we expect the adequacy of randomisation to compensate for any variation of effect between ethnicities.

The authors acknowledge the limitations of a single masked study, but have made every effort to reduce investigator bias. As the IMP is no longer visible inside the eye after approximately 8 weeks, it is unlikely that the investigators will be aware of the treatment allocation of the participant at the time of the primary and secondary outcome assessments. The trial team considered using an independent assessor of the primary outcome measure at 6 and 12 months, but felt that there was insufficient evidence to suggest this was necessary and that it added additional unjustifiable cost to the study.

Furthermore, by 1) masking the operating surgeon to the treatment allocation until the end of the surgical procedure and 2) explicitly defining the clinical findings and adverse events and adhering to rigid management protocols, (for example, for an IOP rise), we have limited investigator bias as much as possible.

In summary, this is the first randomised controlled clinical trial to investigate the use of an adjunctive slow-release dexamethasone implant in patients undergoing vitrectomy surgery for retinal detachments with proliferative vitreoretinopathy.

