## Methods/design

This phase III single-masked randomised control study aims to determine whether there is a beneficial effect in using a slow-release dexamethasone preparation as an adjunctive treatment at the time of surgery in patients with established PVR following rhegmatogenous retinal detachment.

The 140 patients are to be divided into two equal groups (treatment and control arm). They are recruited for the study if they satisfy the inclusion and exclusion criteria. Participants are masked to their treatment allocation until completion of the study and the operating surgeon is masked until the time of IMP delivery.

Both groups will receive standard surgical treatment and routine preoperative and postoperative treatment and care comprising standard 3 port *pars plana* vitrectomy (or gel trimming if the eye was previously vitrectomised) and internal identification of retinal breaks; peeling of anterior and posterior epiretinal membranes and removal of subretinal membrane if required; relief of traction by retinectomy or placement of a scleral buckle at the operating surgeon’s discretion; retinopexy to retinal breaks and retinectomy edge by cryotherapy or laser; intraocular tamponade using 1300 or 5000 centistoke silicone oil. Intra-oil medication, the IMP, will be administered through a sclerostomy prior to wound closure in the treatment group.

A check for perfusion of the optic nerve head immediately after the injection of the IMP will be performed, along with digital indentation to confirm a satisfactory IOP once all scleral ports have been sutured. Biomicroscopy will be performed the following day to confirm the position of the implant.

If a patient is rendered aphakic as part of the operative procedure and they have been randomised to receive the IMP, the study treatment will not be given
[30,31], but the patient will still be followed up as part of the study.

Removal of silicone oil (combined with cataract extraction plus intraocular lens implantation when applicable) will be planned for 3 to 5 months after primary surgery. On removal of oil, a second dexamethasone implant will be administered with performance of the same aforementioned safety monitoring. Again, if a patient is rendered aphakic or an anterior chamber intraocular lens is inserted as part of the operative procedure, and the patient has been randomised to receive the IMP, the study treatment will not be given. The patient will still be followed up as part of the study.

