### Study visits and assessment schedule

Postoperative study visits will not differ from the routine schedule for vitreoretinal procedures at the study site for the first 6 months that is day 1, day 10, day 30, 3 months and 6 months. Further assessments will be scheduled for 9 and 12 months post initial surgery. The time window allowed around these scheduled visits will be as follows: day 10 (+/- 3 days), day 30 (+/- 7 days) and months 3, 6, 9 and 12 (+/- 14 days). At each scheduled postoperative study visit, a full ophthalmic assessment will be completed, including slit lamp biomicroscopy (with indirect binocular ophthalmoscopy when required) and recording of parameters including ETDRS visual acuity, Goldman applanation tonometry, anterior segment assessment and retinal attachment status. SD-OCT will be used to record the central foveal thickness and total macula volume. An additional study visit to assess IOP has been included in the protocol schedule at day 60 postoperatively following both the study vitrectomy and the removal of oil procedure.

Silicone oil removal will not be considered a reoperation and there will be routine subsequent follow-ups until the patient can return to the study visit schedule. Other vitreoretinal interventions (with the exception of external retinal laser treatment, and macula ERM peel) over the trial period will be considered reoperations and recorded as such. Postoperative visits related to reoperations, or any other attendance outside the study visit schedule, will be recorded as 'unscheduled visits’. Case report forms (CRFs) identical in composition to the study scheduled visit CRF will be completed and included in the data analysis on completion of the study.

Following the final study visit at 12 months, participants will be discharged back to the care of their general practitioner. Participants requiring ongoing ophthalmic care will be followed up by their admitting consultant or will be under the care of a more appropriate specialist consultant, for example, a glaucoma specialist.

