### Masking

Participants are masked to their treatment allocation until their completion of the study. The operating surgeon is masked until the end of the procedure just prior to sclerostomy closure, to avoid any bias regarding surgical management. It is not possible to mask the investigators actively as the IMP may be visible during posterior chamber assessment until its degradation. A placebo vehicle was not used as a comparator as it was deemed unethical due to lack of safety data, and the scientific justification is that the treatment group can be compared to the standard care group.

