### Outcome measures

#### Primary

The primary outcome will be whether there is stable anatomic reapposition of the retina to the retinal pigment epithelium without additional vitreoretinal intervention in the absence of an internal tamponade agent at 6 months post study vitrectomy.

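### The reassurance that assessors will not know the allocation at 6 months counts only the first implant; the second, given at oil removal, can still be visible at the primary assessment

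*Protocol article*

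**What the plan says.** The article describes a single-masked trial. Participants do not know their arm, and the operating surgeon does not know it until implant delivery. For the other investigators, the Masking section concedes: "It is not possible to mask the investigators actively as the IMP may be visible during posterior chamber assessment until its degradation". The same section explains that no placebo vehicle is used.

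The Discussion then offers a mitigation: "As the IMP is no longer visible inside the eye after approximately 8 weeks, it is unlikely that the investigators will be aware". It makes this claim about knowledge of the arm when either the primary or the secondary outcomes are assessed. The next sentence reports that an independent assessor of the primary outcome was considered and not adopted, for want of evidence of need and on grounds of cost.

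The Methods/design section says of silicone oil removal that it "will be planned for 3 to 5 months after primary surgery. On removal of oil, a second dexamethasone implant will be administered". The section on management of intraocular pressure allows that operation to be postponed by up to 4 weeks. The primary outcome is stable reattachment without further vitreoretinal intervention, "in the absence of an internal tamponade agent at 6 months post study vitrectomy".

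**The concern.** The 8-week argument is sound for an implant placed at the vitrectomy. It does not consider the implant placed months later, shortly before the primary assessment. Only treated eyes can carry an implant, so an examiner who sees one knows the arm.

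The primary outcome contains judgement. Someone must read whether the retina is attached, and someone must earlier have decided whether to reoperate. Eyes that carry a second implant have had their oil removed. Unless they have had a reoperation, the attachment reading decides success or failure in exactly those eyes. If the reading is made with the allocation in view, detection bias in the primary result cannot be ruled out on the ground that the article gives.

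**Working it through.** **Inputs from the protocol article**
- Visibility: about 8 weeks, taken as 56 days (Discussion).
- Second implant: at oil removal, planned for months 3 to 5 (Methods/design).
- Postponement: up to 4 weeks, 28 days (Management of intraocular pressure).
- Primary assessment: month 6; visits at months 3, 6, 9 and 12 have a ±14-day window (Study visits and assessment schedule).
- One month = 365.25/12 = 30.44 days, so month 6 is day 182.6.

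**Step 1. The article's own argument.** The first implant is visible to day 56, or 56/30.44 = month 1.84. That is well before day 182.6, so for the first implant the statement follows.

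**Step 2. The second implant.** Last visible day = removal day + 56.

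| Oil removed at | Removal day | Visible to day | Visible to month |
|---|---|---|---|
| month 3 | 91.3 | 147.3 | 4.84 |
| month 4 | 121.8 | 177.8 | 5.84 |
| month 5 | 152.2 | 208.2 | 6.84 |
| month 5 + 4 weeks | 180.2 | 236.2 | 7.76 |

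The period in which visibility ends spans the 6-month visit.

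**Step 3. Cut-off.** The implant is still visible if removal took place later than (visit day − 56).
- Nominal visit: 182.6 − 56 = day 126.6, month 4.16.
- 14 days early: 168.6 − 56 = day 112.6, month 3.70.
- 14 days late: 196.6 − 56 = day 140.6, month 4.62.

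**Step 4. Share of re-implanted eyes.** The article gives no distribution of removal times. Assume an even spread over months 3 to 5 with no postponement, a span of 152.2 − 91.3 = 60.9 days. Share visible = (152.2 − cut-off day)/60.9.
- Nominal visit: 25.6/60.9 = 42%.
- 14 days early: 39.6/60.9 = 65%.
- 14 days late: 11.6/60.9 = 19%.

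At the nominal visit, taking visibility as 6 or 10 weeks instead of 8 gives 19% or 65%.

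**Step 5. Share of the treated arm.** The second implant is omitted for aphakia, for an anterior chamber lens and for uncontrolled pressure, and an eye with oil still in place has not had one. If a fraction r of the arm is re-implanted, the share is 0.42 × r. The article does not give r. With r = 1 the share is 42%. With r = 0.76 (an illustration, borrowing the planned success rate of 100% − 24%) it is 32%.

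**Step 6. Later visits.** The latest visibility on the protocol's timing is month 7.76. The 9-month window opens at (9 × 30.44 − 14)/30.44 = month 8.54. By months 9 and 12 no implant given on schedule should be visible.

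**The case against.** **The trial does not claim assessor masking as a design feature.** It calls itself single-masked, says investigators cannot be actively masked, and acknowledges the limitation. This is true, and it confines the error to one argument in the Discussion. But that argument extends explicitly to the primary assessment, where the trial's own schedule undoes it.

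**Much of the protection remains.** A reader might infer that masking does not exist at 6 months. The documents do not support that. Under the even-spread assumption, 58% of re-implanted eyes show nothing at the nominal visit, and eyes without a second implant show nothing either. Nor is 42% a share of the treated arm; it applies to re-implanted eyes only.

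**Postponed eyes.** If every removal were delayed by the full 4 weeks, the same method would give 88% at the nominal visit. I do not rely on this. Eyes whose pressure stays high lose the second implant, so those delayed longest may be the least likely to receive one.

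**Error inflation.** A reader might also infer a quantified false-positive rate. With 66 per arm and failure truly 49% in both, moving 5 points of failures to success in the treated arm would raise the two-sided error from 5% to about 9%, and 10 points to about 21%. No figure in the article supports either shift. Oil status and a past reoperation are recorded facts that cannot be re-read at the visit; the attachment reading can be influenced, as could the earlier decision to reoperate.

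**Fading does not restore masking.** This cuts the other way. The surgeon learns the arm at delivery, and biomicroscopy the next day checks the implant's position after both insertions. The article does not say who performs the 6-month assessment, so how far such knowledge carries over is unknown.

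**Conclusion.** The Discussion's statement is wrong as applied to the 6-month primary assessment. On the article's own timings, the second implant can be visible until about month 6.8, or month 7.8 with the permitted postponement. About 42% of re-implanted eyes would show it at a nominal visit (19% to 65% across the window), given 56 days of visibility and evenly spread removals. The share of the treated arm is lower by an amount the article does not fix.

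Assessor masking at 6 months therefore cannot be relied on. At 12 months the visibility argument holds, although knowledge gained earlier may persist. The size and direction of any resulting bias cannot be derived from the document. The decision against an independent assessor follows directly after the statement, but the reasons given there are lack of evidence of need and cost; one cannot say that it rests on the visibility claim alone. The sample size is not affected.

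**What to change.** 1. Correct the Discussion sentence. Say that investigators may know the allocation at the 6-month primary assessment because of the second implant. Say that the trial is single-masked: participants throughout, the operating surgeon only until implant delivery. Name unmasked assessment as a limitation of the primary result. Participant-masked only would be the wrong description, since it drops the surgeon masking.
2. Pre-specify the same composite (retina attached, no tamponade, no reoperation) at the existing 9-month visit as a supportive sensitivity analysis, not as a condition for claiming benefit. State what it does and does not do: it removes visibility of the implant at the assessment, but not memory of the allocation or the effect of earlier reoperation decisions.
3. Optionally, record at the 6-month visit whether an implant was seen and report the frequency descriptively. The treatment comparison should not be split by this flag: only treated eyes can have it, and it arises after randomisation, so such a split would not be a randomised comparison.

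The cost is a less favourable masking statement, one extra analysis and, if wanted, one tick box on the case report form. No new visit is needed.

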## Trial status

The authors confirm that the trial was in active recruitment at the time of manuscript submission.

## Abbreviations

CRF: Case report form; IMP: Investigational medicinal product; IOP: Intraocular pressure; ITT: Intention to treat; MHRA: Medicines and healthcare products regulatory agency; PIL: Participant information leaflet; PVR: proliferative vitreoretinopathy; REC: Research and ethics committee; SD-OCT: Spectralis domain optical coherence tomography; ETDRS: Early treatment diabetic retinopathy study; ERM: Epiretinal membrane.
